
#### Participant timeline

A research member will screen the operating list for any eligible patients. When identified, the patient will first be encountered for the presentation of the research project and possible recruitment. This first encounter will be at least one hour before the scheduled surgery time and will be in the surgical day care unit or in the unit in which the patient is hospitalized. When consent is obtained, patients will first complete a demographic questionnaire. They will then be transported to the induction room for the performance of the plexus block, as previously described. Once the block is completed, patients will remain monitored in a suitable area with appropriate surveillance (induction room, operating room (OR), recovery room) until surgery. The independent research assistant will assess the sensory and motor loss at 10, 20 and 30 minutes (see Fig. 1).

**Fig. 1 Fig1:**
[figure not shown]
Template of the schedule of enrolment, interventions and assessments. Summary of the study period for each participant, from the recruitment to the close-out

#### Sample size

We decided to conduct a non-inferiority trial with the aim of demonstrating that performance time for the RCB approach is no longer than for the coracoid ICB approach. On the basis of a recent study [15], we established that the performance time for the coracoid ICB approach is 5 min 36 s, with 45 s of visualization time. On the basis of the feasibility trial recently conducted, needling time for the RCB approach is 3 min 42 s [11]. If we use the same imaging time of 45 s, we expect a performance time of 4 min 29 sec for the experimental approach. The standard deviation used for both groups was 2 min 18 s, as reported in the literature [15]. We deemed that a time superiority of 5% would be significant. In other words, RCB performance time will be deemed non-inferior to ICB if the upper margin of the 95% confidence interval created around RCB performance time is under the ICB performance time plus 5%. When using these hypotheses to conduct a non-inferiority analysis, a calculated sample size of 49 patients per group will be required to provide statistical power of 0.90 and one-sided type I error of 0.05. To compensate for potential dropouts or inadequate procedures, we will aim for a sample size of 55 patients per group.

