#### Statistical methods

Analysis of the primary outcome: performance time will be analyzed with a non-inferiority test of the averages, with the objective of finding that the experimental RCB approach takes no longer to perform than the coracoid ICB approach.

The secondary outcomes will all be analyzed using superiority analysis. For continuous data or ordinal data with >8 categories, data will be compiled as average and standard deviation. If data are parametric, Student’s *t* test will be used and if not, the Mann-Whitney test will be used. For dichotomous data (block success, use of neurostimulation), the chi square or Fisher exact test will be used if n >5 or is not >5, respectively. Finally, for ordinal data the chi square test will be used if data are parametric, otherwise the Mann-Whitney test will be used.

Subgroup analysis will be conducted to evaluate if higher BMI influences the outcomes of performance time, needle visibility, number of needle passes and needle angle. Patients will be divided in two groups (of those with higher and those with lower BMI than the average BMI of all recruited patients) and analyzed according to their subgroup. If data are missing or if any patients drop out of the study, data will be analyzed using the intention-to-treat principle.

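### The written non-inferiority rule puts a confidence interval around the RCB mean alone, so it is not the two-arm, one-sided 5% test for which 49 per group was calculated

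*Protocol article*

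**What the plan says.** The only explicit success criterion for performance time is in the protocol article, Sample size. After setting the tolerance at 5% of the comparator's time ("We deemed that a time superiority of 5% would be significant"), it says RCB will be deemed non-inferior "if the upper margin of the 95% confidence interval created around RCB performance time is under the ICB performance time plus 5"%.

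The next sentence says that 49 patients per group are "required to provide statistical power of 0.90 and one-sided type I error of 0.05". The Methods part of the Abstract repeats the 49, the 0.90 and the one-sided 0.05. The enrolment target is 55 per group.

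Statistical methods says only that "performance time will be analyzed with a non-inferiority test of the averages", with the aim of showing that RCB takes no longer than coracoid ICB. It gives no interval, confidence level or margin.

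**The concern.** Three things in these passages do not fit together.

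- **One arm's variance is missing.** The rule sets an interval for RCB against a single ICB number. If that number is the trial's ICB mean, it is itself estimated from about 49 patients, and leaving out its error makes the rule too easy to pass. If it is the literature figure, the comparison is no longer between randomised arms.
- **The level does not match.** The upper limit of an ordinary two-sided 95% interval is a one-sided 2.5% criterion. The sample size uses one-sided 5%.
- **The rule is not the powered test.** The stated 49 per group needs the variance of both arms.

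The rule decides the primary conclusion. With the observed ICB mean, its error runs in favour of the new technique.

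**Working it through.** **Inputs (protocol article, Sample size)**
- ICB mean: "the performance time for the coracoid ICB approach is 5 min 36 s, with 45 s of visualization time", so 336 s in total.
- RCB mean: "we expect a performance time of 4 min 29 sec for the experimental approach", so 269 s.
- SD: "The standard deviation used for both groups was 2 min 18 s", so 138 s.
- Margin: 5% of 336 s = 16.8 s (0.28 min), so the limit is 352.8 s. Distance from the expected RCB mean: 352.8 − 269 = 83.8 s.
- One-sided alpha 0.05 (z = 1.645); power 0.90 (z = 1.282).

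**Step 1: reproduce the 49**
- Two-arm contrast mean(RCB) − 1.05 × mean(ICB): n = (1.645 + 1.282)² × 138² × (1 + 1.05²) / 83.8² = 48.8, so 49.
- Difference in means against a fixed 16.8 s margin: n = 2 × (1.645 + 1.282)² × 138² / 83.8² = 46.4, so 47. The t-based version gives 48, or 49 if the RCB time is rounded to 4.5 min.
- The same two formulas at one-sided 2.5% give 60 and 57, which do not match.
- One arm against a constant: (1.645 + 1.282)² × 138² / 83.8² = 23.2, so 24. At one-sided 2.5% it is 28.5, so 29. Neither matches.

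The stated size therefore belongs to a two-arm calculation at one-sided 5%. The exact formula cannot be identified.

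**Step 2: type I error of the written rule, using the observed ICB mean**

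The rule passes if RCB mean + c × SD/√n < 1.05 × ICB mean. When RCB is truly 5% slower, RCB mean − 1.05 × ICB mean is centred on zero with standard error SD × √((1 + 1.05²)/n). SD and n cancel, so the error is Φ(−c/√(1 + 1.05²)) = Φ(−c/1.45). With a fixed 16.8 s margin it is Φ(−c/√2).

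| Reading of the 95% limit | 1.05 × ICB mean | ICB mean + 16.8 s |
|---|---|---|
| Two-sided interval, c = 1.96 | 8.8% | 8.3% |
| One-sided bound, c = 1.645 | 12.8% | 12.2% |

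Simulation with t limits at n = 49 gives 8.6% and 12.6% for the 1.05 form. At n = 55 the figures are again 8.6% and 12.6%, so the larger enrolment does not help.

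If the two techniques take exactly the same time, the standard error of one arm at n = 49 is 138/7 = 19.7 s, and that of the contrast is 19.7 × 1.45 = 28.6 s. The written rule with c = 1.96 then passes with probability Φ((16.8 − 1.96 × 19.7)/28.6) = 22%. A correct one-sided 5% test passes with probability Φ(16.8/28.6 − 1.645), about 15%.

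**Step 3: the literature reading**

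If the comparator is the constant 336 s, the error is 2.5% (two-sided interval) or 5% (one-sided bound), but only if the true ICB mean in this trial is 336 s. To show the range, assume it is 10% lower, 302.4 s. An RCB mean at the margin is then 1.05 × 302.4 = 317.5 s, and it passes with probability Φ((352.8 − 317.5)/19.7 − 2.01), about 41%. If it is 10% higher, 369.6 s, the probability is below 0.01%.

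**Step 4: two-arm alternatives**
- One-sided 5% bound on the 1.05 contrast, n = 49: power = Φ(83.8/28.6 − 1.645), about 0.90; simulated type I error 5.0%.
- Two-sided 95% interval (one-sided 2.5%), n = 49: power 0.83 for the 1.05 contrast and 0.85 for the fixed margin. With 55 analysed per group it is about 0.87 and 0.89.

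**Side point.** The RCB components ("needling time for the RCB approach is 3 min 42 s" plus 45 s) add to 4 min 27 s, not 4 min 29 s. With 267 s the Step 1 formulas give 47 and 45. The type I error results do not depend on this.

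**The case against.** The best defence is that the sentence is loosely worded. It sits under Sample size and restates the 5% margin. The section that names the analysis calls for a non-inferiority test of averages, which most naturally means a two-arm test, and such a test agrees with the one-sided 0.05 and with 49 per group. A separate analysis plan may also give the details.

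Much of this is fair: a two-arm interval may well have been intended. But the criterion is stated, not left open, and Statistical methods supplies no interval, level or margin to replace it. Even if the 95% interval is moved to the difference, its upper limit conflicts with the stated one-sided 5% unless a one-sided bound is meant.

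Three stronger inferences are tempting, and the document does not support them:
- *That the error rate simply is 9–13%.* This holds only if the comparator is the observed ICB mean, and it merges two readings of the interval. The higher end needs a one-sided 95% bound, and on that reading the mismatch of levels disappears. The two charges cannot be combined.
- *That 49 arises only from the 1.05 contrast.* A t-based fixed-margin calculation gives 48, or 49 with modest rounding, and the article names no formula.
- *That the trial is underpowered.* Power falls below 90% only if the repair keeps a two-sided 95% interval. As written, the rule has power of about 0.94 (two-sided limit) or 0.96 (one-sided bound) at 49 per group, because it is too lenient.

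**Conclusion.** The rule is wrong as written and must be reconciled with the test that was sized. Read most directly, with an ordinary two-sided 95% interval and the observed ICB mean, its one-sided type I error at the margin is about 8–9% against the stated 5%. With a one-sided 95% bound it is about 12–13%. With the literature value as comparator there is no single error rate, and the randomised control arm plays no part in the decision. These figures assume approximately normal means and the same SD in both arms, as the sample size does; given that, they depend very little on n.

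A reader should not conclude that the investigators chose to ignore control-arm variance, or that the final analysis will be inflated. What is established is that the only written criterion and the stated error rate and sample size describe different tests.

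**What to change.** Replace the criterion in Sample size, and repeat it in Statistical methods, with: RCB is non-inferior if the one-sided 95% upper confidence bound (the upper limit of the two-sided 90% interval) for mean(RCB) − 1.05 × mean(ICB), computed with the variance of both randomised arms, is below zero. This form follows the plus-5% wording, holds type I error at 5% and keeps about 90% power at 49 per group.

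A fixed 0.28 min margin on the difference in means is a different test. It ties the margin to the literature mean and gives a different sample size (46.4 against 48.8 before rounding up). It should not be offered as interchangeable; one form has to be chosen.

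If a two-sided 95% interval on the two-arm contrast is preferred, restate the type I error as one-sided 2.5% and the power as about 83–85% at 49 analysed per group, or about 87–89% at 55.

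The cost is one sentence, with no extra patients or data. At submission a quarter of the calculated sample had been recruited and no interim analysis was planned, so from that point the rule could still be fixed before the final analysis.

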#### Recruitment

As most of the patients will not have been seen previously at the preoperative clinic, we will recruit the patients on the same day as they undergo surgery. The patients will first meet the research team on the surgical day care unit or on the unit where the patient is waiting for surgery. A member of the research team or the attending anaesthesiologist will see the patient at least one hour before the planned surgery schedule and will explain the research project. The patient will receive the consent form at least one hour before surgery and will be given time to read, assess and ask questions before deciding whether or not to participate. The patient will be assured that the quality of care and professionalism will not be affected by refusal to participate.

## Methods

### Assignment of interventions

#### Allocation: sequence generation

Participants will be randomly assigned to either the control or experimental group with a 1:1 allocation ratio as per a computer-generated randomization schedule stratified by sites using permuted blocks of random sizes. The block sizes will not be disclosed, to ensure concealment. Stratification by site will be of particular interest because in this current pre-trial state, one centre mostly uses the retroclavicular approach while the second one uses the infraclaivuclar approach.

#### Allocation concealment mechanism

Sequentially numbered, opaque, sealed envelopes will be used to ensure concealment until enrolment is confirmed. These envelopes will be kept in the locked research assistant office and the recruiting members will have to contact this research assistant to randomize the patient. When the numbered envelope is opened, the patient is automatically included in the analysis and the numbers on each envelope ensure that all patients are enrolled after being randomized. A recruitment log will be created and exclusion will be justified for each patient excluded.

#### Blinding (masking)

In this trial, only the outcome assessor for the motor block and sensory block will be blinded. For obvious reasons, it is not possible to blind the anaesthesiologist performing the block. Moreover, the current setup at the included hospitals does not allow the blinding of the anaesthesiologist supervising the surgery. Thus, the anaesthesia team in the case of block failure will not be blinded. Patients will not be blinded either, as we opted not to fake a plexus block with another needle entry point for organizational reasons and to avoid patient discomfort. However, the primary outcome of performance time should not be affected by patient blinding. Considering that the anaesthesiologist will not be blinded, we did not think it necessary to blind the statistician as, even if blinded, the risk of contamination would be too high.

Discomfort during the procedure and the quality of the motor block and sensory block at 10, 20 and 30 minutes will be assessed by a blinded investigator. Another anaesthesiologist, resident or respiratory therapist will be in charge of evaluating sensory and motor function with pre-established indications to ensure competency. To reinforce blinding, chlorhexidine will be applied over the two theoretical needle entry points and two bandages will be applied.

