##### Secondary outcome measures

Imaging time: will be measured in minutes and corresponds to the time interval between contact of the US probe with the patient skin and the acquisition of a satisfactory image.Needling time: will also be measured in minutes, from the start of the skin wheal to the removal of the block needle from the tissues.Sensory loss at 10, 20 and 30 minutes: will be assessed in the territory of the radial (lateral aspect of the dorsum of the hand), median (volar aspect of the index), ulnar (volar aspect of the fifth finger), musculocutaneous (lateral aspect of the forearm), and medial cutaneous nerve of the forearm (medial aspect of the forearm) distributions using a 3-point score, where 0 = normal sensation, 1 = diminished sensation to pinpricks (hypoesthesia), and 2 = loss of sensation to pinpricks (analgesia). The sum of five scores on a maximum of 10 will be the sensory-loss final score. An independent, blinded, research assistant will complete the sensory assessment at 10, 20 and 30 minutes.Motor block at 10, 20 and 30 minutes: motor function will be tested (0 = normal strength, 1 = weakness, 2 = paralysis) for the radial (wrist extension), median (thumb-fifth finger opposition), ulnar (fifth finger abduction), and musculocutaneous (elbow flexion) nerves. The sum of the four scores on a maximum of 8 will be the motor block final score. An independent, blinded, research assistant will complete the motor assessment at 10, 20 and 30 minutes.Success of plexus block: success is a dichotomic variable answered by yes or no. Success is defined as the completion of surgery without the need for additional LA infiltration, intravenous narcotics, or general anaesthesia. However, light sedation is allowed if deemed necessary by the anaesthesiologist. Light sedation includes midazolam 1 to 4 mg intravenously, fentanyl up to 1mcg/kg. A minimum sensory score of 9/10 will be necessary to proceed to surgery without additional LA infiltration. Patients with an overall sensory score under 9/10 at 30 min will be offered general anaesthesia or supplemental blocks.Total anaesthesia time: is measured in minutes and defined as the sum of performance time and time to achieve a minimum sensory score of 9/10. It is the time for readiness for surgery.Number of block needle passes: is defined as a unit of 1, 2, 3, etc., and is the number of times the block needle will have to be realigned on the skin in order to achieve its final positioning goal under the axillary artery.Needle visualization: procedures will be videotaped and reviewed simultaneously after study completion by 2 independent anaesthesiologists skilled in US-guided regional anaesthesia using a 5-point Likert scale to rate needle visibility (1 = very poor, 2 = poor, 3 = fair, 4 = good, 5 = very good). Needle visibility will be evaluated twice. First, for RCB, assessment will be made when the needle tip is seen 1 cm after crossing the clavicle acoustic shadowing. For the coracoid ICB, the first assessment will be at a needle tip depth of 1 cm. The second needle visibility assessment will be immediately before the local anaesthetic injection, when the visibility is theoretically optimized.Needle angle: using the same videotape that we used for the evaluation of the needle visibility, we will note the angle between the needle and the upper side of the ultrasound image. It will be a continuous outcome ranging from 0 to 90 degrees.Neurostimulation use: neurostimulation is accepted if needed. However, its use other than for a safety sentinel (defined by <0.3 mA) will be recorded for subsequent analysis. It will be a dichotomous outcome.Pain during the procedure: immediately after block completion, patients will be asked to rate their discomfort associated with the procedure using a 10-cm visual analogue scale (0 = no pain, 10 = worst pain imaginable) by an independent and blinded outcome assessor.Early and late complications: the incidence of needle-induced paresthesia, vascular puncture, Horner syndrome, dyspnea, and symptoms of LA toxicity will be noted. All patients will be contacted 48 hours after surgery to ask for any delayed complications, such as dyspnea, paresthesia, weaknesses, pain at the puncture site or haematoma. Patients with complications will be followed up by our research group and a consultation in neurology may be sought.

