## Methods

### Data collection, management and analysis

#### Data collection methods

De-nominalized demographic data will be collected by an independent investigator. During the procedure, a standardized data collection document will be used to ensure that all data points are noted and are available for future statistical analysis. For every plexus block, at least two people (operator plus research assistant) will be required for data collection and the research assistant will be responsible for time measurement using a chronometer. Because patient follow up is maintained only up to 48 hours after the surgery, patient retention is not expected to be an issue. Demographic data will include a phone number to allow communication after discharge from the hospital. A presentation to the anaesthesia department and peripheral participating centres will be done to explain the project and pertinent documents.

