### Harms

Potential harms are mentioned to the patient as standard before any regional anaesthesia, including risk of pneumothorax, transient or permanent nerve injury, vascular puncture, infections, Horner syndrome or failed plexus block. This practice will be maintained throughout this trial. Any adverse effects or complications will be compiled in the data collection form, but we do not expect to have enough power to find any significant differences. In the feasibility study, no significant or permanent harms were inflicted on the patients with the experimental method. Moreover, we expect better visibility with the RCB approach, which could be associated with reduced risk of complications.

If important harms or concerns about patient safety are noted, we will report to the research group and ethics committee for evaluation on the continuation of the trial. We will also act accordingly in seeking appropriate medical attention if deemed necessary.

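### Early and 48-hour complications are collected outside the protocol's stated blinding, although a blinded assessor already sees every patient at 10, 20 and 30 minutes

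*Protocol article*

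**What the plan says.** All references are to the protocol article.

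- **Status of the outcome.** Objectives names early and late complications among the comparisons. Secondary outcome measures lists them, and Statistical methods puts all secondary outcomes under superiority analysis.
- **How they are collected.** For the early events, "the incidence of needle-induced paresthesia, vascular puncture, Horner syndrome, dyspnea, and symptoms of LA toxicity will be noted". Patients are then contacted 48 hours after surgery and asked about delayed complications, with examples (dyspnea, paresthesia, weakness, puncture-site pain, haematoma). Neither sentence names the person who records or calls, or says whether that person is blinded.
- **Who is blinded.** Blinding (masking) states: "In this trial, only the outcome assessor for the motor block and sensory block will be blinded". Its second paragraph widens this by one item, procedural discomfort, in a sentence that goes on to name an investigator unaware of allocation: "Discomfort during the procedure and the quality of the motor block and sensory block at 10, 20 and 30 minutes will be assessed by a". For patients: "Patients will not be blinded either, as we opted not to fake a plexus block with another needle entry point". The operator and the anaesthesiologist supervising surgery are also unblinded.
- **Who handles the form.** Data collection methods says "at least two people (operator plus research assistant) will be required for data collection" at every block. Harms says "Any adverse effects or complications will be compiled in the data collection form".
- **Expectation.** Harms adds that "we expect better visibility with the RCB approach, which could be associated with reduced risk of complications".

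**The concern.** Several listed complications depend on how they are looked for. Dyspnea, paresthesia, weakness and site pain vary with whether and how the patient is asked, and a mild Horner syndrome is easily missed if nobody checks. When the person asking knows the technique, a difference in recorded counts may reflect a difference in looking.

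The protocol protects its motor and sensory scores against this. It uses a separate assessor at 10, 20 and 30 minutes, with skin preparation and bandages at both possible entry sites. Complications are not assigned to that person, although some could be seen or asked about at the same visits.

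At stake is the reading of the safety results. The Abstract's discussion hopes that RCB might be adopted widely. Harms admits that power is too low to find differences in complications, so readers will rely on the raw counts, which are what uneven ascertainment distorts.

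**Working it through.** **Step 1. Who ascertains what, from the text.**

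| Item | Recorder named? | Inside stated blinding? |
|---|---|---|
| Sensory and motor scores, 10/20/30 min | Yes, blinded assistant | Yes |
| Pain during the procedure | Yes, blinded assessor | Yes |
| Early complications | No | Not listed |
| 48-hour complications | No | Not listed |

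The blinding section lists what is blinded, and complications are not on the list. That much is stated. That the operator and bedside assistant record early complications is an inference from three places: the blinding list, the two-person data collection at each block, and the entry of complications on the data collection form. The only task given explicitly to the research assistant in that section is timing. The sentence "Patients with complications will be followed up by our research group" concerns what happens once a complication is known, so it does not settle who detects it.

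**Step 2. Which complications a blinded assessor could take over.**

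- Horner syndrome, dyspnea and toxicity symptoms present at 10, 20 or 30 minutes: yes.
- Vascular puncture, needle-induced paresthesia and symptoms during injection: no. They occur before the first blinded visit.
- Persisting paresthesia at 10 to 30 minutes: no. It cannot be interpreted in a limb that is being deliberately blocked.
- 48-hour symptoms: partly. The caller can be kept unaware of allocation, but the patient is not.

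**Step 3. Size, by illustration.** The plan has no figure on complications to reproduce. The only input from the documents is the target of 55 per group (Sample size). Rates and under-recording are assumptions.

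Let p be the true rate in both arms and s the share of RCB events recorded, with all ICB events recorded. The apparent difference is p(s - 1).

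- p = 15%, s = 0.75: 0.15 × 55 = 8.25 events in each arm; recorded with RCB 0.75 × 8.25 = 6.19; difference (6.19 - 8.25)/55 = -3.75 points, about two events.
- p = 5%: -1.25 points. p = 30%: -7.5 points.
- Sampling error at p = 15%: sqrt(2 × 0.15 × 0.85/55) = 0.068, or 6.8 points. The illustrative bias is about half of one standard error (3.75/6.8 = 0.55).

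Chance of a significant result favouring RCB when there is no true difference (two-sided 0.05, 55 per arm, normal approximation):

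| True rate | s = 0.8 | s = 0.6 | s = 0.5 |
|---|---|---|---|
| 10% | -2 points; 5.5% | -4 points; 12% | -5 points; 17% |
| 20% | -4 points; 8% | -8 points; 21% | -10 points; 31% |

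Without bias, the chance in this direction is nominally 2.5%. The formula is Φ[(d - 1.96·se0)/se1], with se0 from the pooled rate and se1 from the separate rates. For 10% against 5%: d = 0.05, se0 = sqrt(0.075 × 0.925 × 2/55) = 0.0502, se1 = sqrt((0.09 + 0.0475)/55) = 0.05, which gives Φ(-0.97) = 0.17. With counts this small the approximation is generous. Summing binomial probabilities over all tables with a two-sided Fisher p of at most 0.05 gives 7.5% for that case.

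**Step 4. Power to detect real differences.** The same formula gives 0.17 for 10% against 5%, 0.31 for 20% against 10% and 0.42 for 10% against 2%. This agrees with the protocol's own concession on power.

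**The case against.** The strongest reply has four parts.

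1. **The recorder is unnamed.** A reader might infer that the protocol has the unblinded operator record the complications of his or her own block and an unblinded person make the call. The text does not say so. The word limiting blinding to the motor and sensory assessor is not strictly exhaustive either, because the next paragraph adds discomfort. Who fills in which field, and the telephone script, often sit in a full protocol or case report form that is not shown. This stands against any claim about who records, and against criticism of a missing script. It does not remove the point: the article gives an explicit account of what is blinded, extends it once, and leaves complications out.
2. **Direction.** A reader might infer bias toward RCB. Harms says only that better visibility could go with fewer complications. The stated hypothesis is similar outcomes apart from needle visibility, and one of the two centres mostly uses the infraclavicular approach. Closer watching of a newer technique could push counts the other way. This stands: direction is plausible, not shown.
3. **Disclosure.** Risk of bias admits performance bias and, for questions about discomfort just after the block and at 48 hours, attention bias that it regards as equal between groups. This is a fair partial disclosure. The same section says the consent form tells patients to expect a shorter, less painful block with RCB, which makes equality less certain. It discusses assessor detection bias only for the motor and sensory block.
4. **Limits of the remedy.** Needling events cannot be blinded, and late symptoms come from unblinded patients. Nothing shows that the blinded assessor is free for a call at 48 hours. This stands and narrows the fix.

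**Conclusion.** The point holds in a limited form. Complications are to be compared between arms, yet they are ascertained outside the blinding that the protocol describes, while a blinded assessor who could record some of them already sees each patient. The resulting bias is possible and partly avoidable; neither its presence nor its direction is established. The documents do not support saying that unblinded staff are assigned to record complications, or that the safety comparison will favour RCB.

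The size depends on assumed figures. Under one-arm losses of 20% to 50% and true rates of 10% to 20%, the apparent difference is -2 to -10 points. The central example of -3.75 points is smaller than its standard error of 6.8 points. It also applies the loss to all complications, whereas only some can be moved to the blinded assessor, so the fix would remove less than the whole. The consequence is mainly a distorted descriptive estimate in an underpowered secondary outcome. The primary outcome is unaffected.

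**What to change.** In Secondary outcome measures and Blinding (masking):

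- State who records each complication and whether that person is blinded.
- At 10, 20 and 30 minutes, after the sensory and motor scores are complete, have the existing blinded assessor record Horner syndrome, dyspnea and local-anaesthetic toxicity symptoms on a fixed checklist. Scoring first protects those scores if the patient reveals the needle site.
- Leave needle-induced paresthesia, vascular puncture and any symptoms during injection with the bedside team, and report them as unblinded.
- At 48 hours, ask the same fixed yes/no questions in both arms, where possible through an existing team member who does not know the allocation. Report late complications as patient-reported and only partly blinded.

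The cost is a change of form and wording, slightly longer assessor visits, and a small risk that patients disclose the needle site. If no unaware team member is available for the call, the fixed questions can still be used, and the lack of blinding should be stated. Recruitment had reached a quarter of the calculated sample size when the article was submitted, so the date of the change should be recorded and earlier patients identified in the report.
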